#### 4.3.2 Secondary criteria

- Hospitalisation proportion and its causes between Day 0 and Day 28 within each group
- Proportion of deaths and their causes between Day 0 and Day 28 within each group
- Intensive care hospitalisation proportion and its causes between Day 0 and Day 28 within each group

---

 Currently, the following criteria are being proposed: SpO2 < 92% in ambient air or 4% reduction in SpO2 since inclusion; respiratory rate > 30 min; heart rate > 130/min; systolic blood pressure < 90 mmHg or diastolic < 60 mmHg; other parameters indicating hospitalisation, in the judgement of the attending physician (for example, unexplained fall, severe digestive problems, reoccurrence or persistent fever > 38.5°C etc.)

- Proportion of patients with a reversion of SARS-CoV2 RT-PCR on a nasopharyngeal swab on Day 7 and Day 14, in each group
- Proportion of patients with a loss of autonomy evaluated by ADLs and IADLs on Day 14 and Day 28
- Changes in CBC, inflammatory markers (please see paragraph **Erreur ! Source du renvoi introuvable.**) and immunological markers (please see paragraph **Erreur ! Source du renvoi introuvable.**) from Day 0 to Day 7 and Day 14 in each group
- Number and proportion of adverse events of grades 1, 2, 3, 4 between Day 0 and Day 14 in each group
- Number and proportion of adverse reactions of grades 1, 2, 3, 4 between Day 0 and Day 14 in each group
- Plasma trough concentration of experimental drugs in the study on Day 7
- Acceptability of the treatment

#### 4.4 Randomisation

There shall be two randomisation lists:

- One list for people not taking renin-angiotensin system blockers (ACEI or ARB) before inclusion.
- One list for people under treatment with renin-angiotensin system blockers (ACEI or ARB) before inclusion.

The randomisation lists shall be created by a statistician at the Clinical Trial Unit (CTU) before the start of the research project. The number of participants in the treatment groups shall be equalised by using a ratio of 1:1 in each arm.

Randomisation shall be stratified by place of residence (home or nursing home). Other stratification factors could be defined over the course of the study by the SAB, if they are deemed necessary.

A document describing the preparation of the randomisation list shall be kept confidential with the CTU. A validated, web-based system shall be used to implement the random allocation to each group.

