### 1.2 Justification

For adults aged 65 years or more affected by the disease COVID-19 at an early phase and without hospitalisation criteria, early treatment could prevent hospitalisation or death. No treatment has currently been validated in this indication (1). The majority of clinical trials for COVID-19 in progress or planned are hospital-centered and enrol patients at a later stage of the disease (2). Optimising treatment at home could reduce the workload in hospitals and improve individual results. This is one of the greatest challenges to be overcome in the weeks to come.

Among risk factors of clinical deterioration in patients with COVID-19, age is described as the most important (3–6). Admission of elderly people suffering from the disease in Intensive Care Units is sometimes limited, justifying the major interest in avoiding the severe forms, which are not necessarily treated in the best way, in the context of an epidemic (7,8).

We are proposing a trial to evaluate the tolerance and efficacy of potential drugs for this indication, while considering the following points:

- Preclinical arguments suggesting an antiviral activity against SARS-CoV-2 already exist for several drugs. Numerous pre-clinical and clinical research projects are in progress on this topic. Ongoing clinical trials must be able to adapt and rapidly change their therapeutic strategies, when new evidence emerges.
- Rapid implementation of a clinical trial for people confined at home poses numerous challenges. Feasibility should be checked, without delaying the evaluation of efficacy.

These points imply the need for a trial comparing the absence of a specific curative treatment (current situation) with experimental curative treatments: (i) starting with available drug candidates, yet allowing consideration of new candidates at any stage; (ii) allowing the interruption of inefficacious treatments (on the basis of futility criteria) or toxic ones.

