## 5 METHODS

### 5.1 Eligibility criteria

#### 5.1.1 Inclusion criteria

- Positive test for SARS-CoV-2 on a nasopharyngeal swab
- Appearance of symptoms <72 hours before taking the nasopharyngeal swab
- Age  $\geq 65$
- Valid person, ambulatory, with full capacity to understand the challenges of the trial
- No hospitalisation criteria according to current guidelines
- Signed, informed consent

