#### 5.1.2 Non-inclusion criteria

##### 5.1.2.1 Autonomy

- Incapable of understanding the meaning of participating in the study (*i.e.*: dementia) or to make a decision to participate (*i.e.*: person under protection of justice, tutorship or guardianship).
- Person with a score  $\geq 7$  on the Rockwood Clinical Frailty Scale
- Chronic illness at a severe stage, with limited life expectancy.

In the particular case of people resident in a nursing home, opinion on inclusion from the coordinating physician of the facility shall be sought, with particular consideration to the environment and the practices at the nursing home.

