### 6.3.1 General information on the statistical techniques used

Qualitative outcomes will be described in tables and graphs as follows: frequency, proportion, standard deviation of the proportion, two-sided 95% confidence interval. Comparisons between arms will use a Chi test or an exact Fisher's test (depending on the outcome distribution) if no adjustment is required or logistic or binomial regression otherwise.

Normality of quantitative outcomes will be checked graphically.

Normally distributed quantitative outcomes will be described in tables and graphs as follows: frequency, mean, standard deviation of the mean, two-sided 95% confidence interval. Comparisons between arms will use a Student's t test if no adjustment is required or a linear model otherwise.

Quantitative non-parametric outcomes will be described in tables and graphs as follows: frequency, median, range and interquartile range. Comparisons between arms will use a Wilcoxon or a Kruskal-Wallis test (depending on the number of strata) if no adjustment is required or a stratified analysis otherwise.

Time-to-event outcomes will be described in tables and graphs as follows: number, probability of event and two-sided 95% confidence interval estimated by the Kaplan-Meier method. Comparisons between arms will use a logrank test if no adjustment is required or a proportional risk (Cox) model otherwise.

Model assumptions will be checked before final adjustment.

Descriptive analyses will be systematically presented globally, by country, stratum and arm.

Comparisons between arms will be systematically performed:

- Without adjustment
- With adjustment on randomisation stratification factors
- With adjustment on randomisation stratification factors and on baseline prognostic factors which distribution could be unbalanced between arms despite randomisation.

Moreover, these adjustments will possibly imply the use of appropriate models not cited here. Their relevance will be discussed depending on the factors nature and distribution.

Details on secondary and exploratory analyses on the primary endpoint and analyses on secondary and exploratory endpoints will be provided in the statistical analysis plan.

The identification of determinants of events will be performed using univariate and stepwise multivariate selection models, which details will be defined in the statistical analysis plan.

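### Age, by the protocol's own account the leading risk factor, is neither a stratification factor nor a covariate fixed in advance for the primary and futility tests; the cost is small and so is the remedy

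*Protocol*

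**What the plan says.** Protocol section 4.4 sets up two randomisation lists, the first being "One list for people not taking renin-angiotensin system blockers (ACEI or ARB) before inclusion" and the second for people who are taking them. It then adds: "Randomisation shall be stratified by place of residence (home or nursing home"). It leaves the list of factors open: "Other stratification factors could be defined over the course of the study by the SAB, if they are deemed necessary". The lists themselves are prepared by a CTU statistician before the research starts.

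Section 1.2 says: "Among risk factors of clinical deterioration in patients with COVID-19, age is described as the most important". Section 5.1.1 admits people aged 65 or over and sets no upper limit.

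Section 6.2.1 fixes the looks (30, 60, 102 and 169 per arm) for participants not taking ACEI/ARB, and section 6.1 places the primary analysis in that group if telmisartan continues to the end. Section 6.3.1 plans every comparison in three versions: unadjusted; "With adjustment on randomisation stratification factors"; and with further adjustment for baseline prognostic factors that may be unbalanced. Section 6.1 makes each primary-endpoint analysis intention-to-treat with missing as failure. It does not say which of the three versions decides whether an arm closes.

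**The concern.** The protocol identifies one dominant prognostic factor and admits a wide range of it, then neither balances allocation on it nor commits to adjusting for it. In the list that drives the arm decisions, prior ACEI/ARB use is constant by construction, so residence is the only named factor at work there.

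The first look has 30 per arm, and all four experimental arms are compared with the same 30 controls. A control group that is older or younger by chance shifts all four comparisons in the same direction. At the final analysis, an unadjusted test carries the age-related variation as noise. The adjusted version in section 6.3.1 may remove it, but age enters that version through observed imbalance, which is a weaker rule than naming it beforehand.

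Age is known at inclusion, so using it needs no new data.

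**Working it through.** **Inputs from the protocol (6.2.1).** Control risk 25%, halved to 12.5%; 80% power; one-sided tests; looks at 30/60/102 with futility alphas 0.65/0.45/0.25; 169 per arm at the end. The final alpha is given only as O'Brien-Fleming, so its value is an assumption below.

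**The plan's own figure.** Per-stage power = Φ{[0.125 − z(1−α)·√(2·p̄(1−p̄)/n)] / √[(0.25·0.75 + 0.125·0.875)/n]}, with p̄ = 0.1875.
- n = 30, α = 0.65: z = −0.385, (0.125 + 0.0388)/0.0995 = 1.647, power 95.0%.
- n = 60, α = 0.45: 95.1%. n = 102, α = 0.25: 94.9%.
- Simulated joint power through all four stages at 169 per arm is 80.4% with a final one-sided alpha of 0.025, and 85.4% with 0.05.

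The design reproduces at 0.025. The power comparison below uses 0.05 and ignores early stopping for efficacy; what matters is the difference between options.

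**Assumptions not in the documents.** Half the participants are aged 75 or over. Control risk by age band is 15%/35% (odds ratio about 3) or 10%/40% (odds ratio 6). Each pair averages 25%, and treatment halves both risks.

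**Age imbalance at 30 per arm.** SD of the difference in the older share = √(2·0.5·0.5/30) = 12.9 points. The exact probability of a difference of at least 20 points is 15.5% for one comparison. By simulation it is about 41% for at least one of the four comparisons with the shared control. If only 30% are in the older band, these become 12% and 33%. At 169 per arm the 95% range of the difference is about ±11 points.

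**Effect on the first decision.** The look-1 boundary lies at −0.385·√(2·0.1875·0.8125/30) = −3.9 points, so an arm is dropped when it looks about 3.9 points worse than control. With odds ratios of 2 to 4, an effective arm is wrongly dropped at this look with probability 4.0% to 4.5% when ages match. If that arm is 20 points older (about an 8% chance per comparison when half are in the older band), this becomes 6.7% to 8.8%. If it is 20 points younger, it falls to 1.7% to 2.8%. Averaged over randomisations it stays near 4.5%. Stratifying by age changes this average to 4.5%, 4.2% or 4.1% for odds ratios of 2, 3 and 4.

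**Variance explained by age.** In the control arm it is (0.10)²/0.1875 = 5.3% or (0.15)²/0.1875 = 12%. Over both arms it is (0.0100 + 0.0025)/0.2969 = 4.2% or (0.0225 + 0.0056)/0.2969 = 9.5%. That is worth about 7 or 16 of 169 participants per arm.

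**Power through all stages (200,000 simulated trials).**

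| Allocation and test | 15%/35% | 10%/40% |
|---|---|---|
| Not age-stratified, pooled z test | 85.4% | 85.5% |
| Not age-stratified, Mantel-Haenszel test by age | 85.9% | 87.1% |
| Age-stratified, Mantel-Haenszel test by age | 86.3% | 87.7% |

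The simulation standard error is about √(0.854·0.146/200,000) = 0.08 points. The total gain is 0.9 or 2.2 points. The adjusted test alone supplies 0.5 of the 0.9 and 1.6 of the 2.2. The split in the milder case is uncertain, because its parts are only a few standard errors.

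**If strata are used but the test ignores them.** The overall one-sided type I error is about 3.6% (15%/35%) or 3.2% (10%/40%), instead of about 4.0%. The test becomes slightly conservative, never liberal.

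**The case against.** Choosing stratification factors is a design judgement, and nothing here is an error or a contradiction. Section 1.2 speaks of COVID-19 patients in general, while this trial already restricts age to 65 or over, so the gradient inside the trial may be milder than assumed. The third version of each comparison in section 6.3.1 can absorb a chance age imbalance. Which version decides is a detail that a statistical analysis plan commonly settles. All of this stands and limits the point to a low-cost improvement. It does not remove it: adjustment triggered by apparent imbalance is not the same as naming age in advance. At the first look the plan's rates imply only about 11 events per comparison (7.5 + 3.75), which gives adjustment alone little to work with.

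A reader might infer four stronger things that the documents do not support.
- **That residence is the only balancing in the whole trial.** The two lists also separate participants by ACEI/ARB use. The statement is true only inside the list that drives the primary decisions.
- **That residence hardly varies.** Eligibility requires a "Valid person, ambulatory, with full capacity to understand the challenges of the trial" and excludes scores of 7 or more "on the Rockwood Clinical Frailty Scale". The nursing-home group may therefore be small. But no share is stated, section 5.1.2.1 provides for these residents, and sections 5.3.2 and 5.3.3 plan sampling and inclusion in nursing homes.
- **That chance imbalance on age is bias.** It is already part of the error rates of a randomised comparison. Shared controls moving all four comparisons together is inherent to the design and comes mostly from outcome variation, not age.
- **That the SAB would choose factors after seeing results by arm.** No section gives it those results. Section 8.2 gives advice on interim analyses to the independent DSMB, and section 10.1 requires an approved amendment for substantial changes to methods. What stands is narrower: a factor added midway balances only later participants and changes what adjustment for stratification factors means.

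**Conclusion.** The point holds as a minor, improvable design choice. Age is ranked first among risk factors, yet it is absent from the strata and enters the analysis only conditionally. Under the assumed gradients the cost is about 1 to 2 points of power, with a 20-point age imbalance in about 15% of single comparisons at the first look. Validity is not affected: there is no bias, no type I error inflation, and the average risk of wrongly dropping an effective arm at the first look barely moves.

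The size rests on an age split and gradient that the documents do not give, and on an assumed final one-sided alpha of 0.05. A milder gradient shrinks it: with an odds ratio of 2, age explains only about 2% of the outcome variance, worth about 3 participants per arm. If telmisartan is dropped and the two groups are pooled (section 6.3.5), ACEI/ARB use also becomes a working balancing factor, but age is still unnamed.

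**What to change.** Before the first inclusion:

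1. In section 4.4, stratify each list by age band (for example 65–74 and 75 or over) as well as by residence.
2. In section 6.1 or 6.3.1, name age as a stratum or covariate in the primary and futility tests, whatever the observed balance, and say that this version decides. In the steeper scenario most of the power gain comes from this step. Stratified allocation adds 0.4 to 0.6 points in the table above and is the part that helps at the 30-per-arm look.
3. Close the list of stratification factors before the start, in place of the clause "Other stratification factors could be defined over the course of the study by the SAB".

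The cost is one setting in the web randomisation system and a few sentences. There would be 8 strata instead of 4 (two lists × residence × age band), so slightly more incomplete blocks if blocks are used. The test must take the strata into account, or it is slightly conservative. No new data and no extra participants are needed.

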## 5 METHODS

### 5.1 Eligibility criteria

#### 5.1.1 Inclusion criteria

- Positive test for SARS-CoV-2 on a nasopharyngeal swab
- Appearance of symptoms <72 hours before taking the nasopharyngeal swab
- Age  $\geq 65$
- Valid person, ambulatory, with full capacity to understand the challenges of the trial
- No hospitalisation criteria according to current guidelines
- Signed, informed consent

#### 5.1.2 Non-inclusion criteria

##### 5.1.2.1 Autonomy

- Incapable of understanding the meaning of participating in the study (*i.e.*: dementia) or to make a decision to participate (*i.e.*: person under protection of justice, tutorship or guardianship).
- Person with a score  $\geq 7$  on the Rockwood Clinical Frailty Scale
- Chronic illness at a severe stage, with limited life expectancy.

In the particular case of people resident in a nursing home, opinion on inclusion from the coordinating physician of the facility shall be sought, with particular consideration to the environment and the practices at the nursing home.

##### 5.1.2.2 Cardiovascular precautions

- An ECG shall be systematically carried out before inclusion.
  - In the case of known Long QT Syndrome, or QTc interval  $\geq 500$ ms in the ECG carried out before inclusion, that person shall not be included in the trial.
  - In the case of a QTc interval between 460 and 500ms in the ECG carried out before inclusion, or any significant anomaly in the ECG such as repeated ventricular extra-systoles, or any significant cardiovascular history giving grounds to believe a predisposition to rhythmic or conduction abnormalities, where the taking of study drugs could bring about conduction or rhythm problems, cardiological opinion shall be systematically sought before any decision to include [SDPM]. If the opinion is such of being capable of inclusion, that person shall be

subject to daily 6 lead ECG monitoring during the first seven days of treatment (please see paragraph **Erreur ! Source du renvoi introuvable.**).

- Blood electrolytes are not to be systematically analysed before inclusion. On the other hand:
  - If the person has benefited from blood electrolytes testing before inclusion (for example, because s/he has sought urgent consultation with symptoms leading to a blood electrolytes prescription), s/he shall not be included if serum potassium were  $>5.5$  mmol/L or  $<3.5$  mmol/L.
  - The results of the blood electrolytes testing performed at the time of inclusion (please see paragraph **Erreur ! Source du renvoi introuvable.**) shall be sent on immediately to the researchers. In cases of significant hypokalaemia, an appropriate decision shall be made in consultation with the researcher, cardiologist and attending physician.

#### 5.1.2.3 Drug intake

- Treatment in progress or taken in the last 30 days by one of the following drugs: piperazine, halofantrine, dasatinib or nilotinib.
- Treatment in progress by: citalopram, escitalopram, hydroxyzine, domperidone, powerful inhibitors of the CYP3A4 isoenzyme of the P450 cytochrome (protease inhibitors of HIV or HCV; azole antifungals; macrolides), powerful inducers of the CYP3A4 isoenzyme of the P450 cytochrome (dexamethasone, phenytoin, fosphenytoin, carbamazepine, oxcarbazepine, eslicarbazepine, rifampicin, rifadin, phenobarbital, primidone, millepertuis).

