| EXCLUSION CRITERIA            | 
 
– Inability to make a decision to participate (dementia, guardianship)
 
– Long QT syndrome, or QTc space > 500 ms
 
– Presence of a pace maker
 
– Heart rate <50 / min
 
– Hyperkalaemia > 5.5 mmol/L or hypokalaemia < 3.5 mmol/L
 
– Treatment with piperazine, halofantrine, dasatinib, nilotinib, citalopram, escitalopram, hydroxyzine, domperidone, potent inhibitors of cytochrome P450 CYP3A4 isoenzyme, potent inducers of cytochrome P450 CYP3A4 isoenzyme repaglinide, azathioprine, 6-mercaptopurine, theophylline, pyrazinamide, warfarin
 
– Hypersensitivity to any of the test drugs or chloroquine and other 4-aminoquinolines, amodiaquine, mefloquine, glafenine, floctafenine, antrafenine, ARB or sartan.
 
– Hepatic porphyria, known obstructive hepato-biliary disease, liver failure (stage ≥ Child-Pugh B), stage 4 or 5 chronic kidney disease (DFG <30 mL/min/1.73 m^2) or person on dialysis, retinopathy, lactose hypersensitivity, abnormalities in galactose metabolism, lactase deficiency, malabsorption syndrome, known glucose-6-phosphate dehydrogenase deficiency, symptomatic gout/hyperuricemia, ileus, colitis or enterocolitis, chronic infection with the hepatitis B virus
 
 |

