#### 1.4.3 Choice of treatments

Among people aged over 65 staying at home, treatments must be acknowledged as being well tolerated and not posing drug interaction problems prohibiting their use with very many people.

For the start of the trial, we have therefore retained hydroxychloroquine, favipiravir, telmisartan and imatinib, which seem to present currently *a priori* the best tolerance profile within this population.

We have neither retained lopinavir/ritonavir, entailing too many digestive problems, nor darunavir/ritonavir nor darunavir/cobicistat, which would be better tolerated, but would lead to too many people being discarded on grounds of possible drug interaction problems.

Hydroxychloroquine has been retained as an experimental treatment, not as a benchmark treatment. The researchers for this trial have monitored the controversy, generated as much by the media as the science regarding the efficacy of hydroxychloroquine. Scientifically, there exists limited and contradictory data and no evidence of its clinical efficacy in this indication. At the media level, it is actually possible that the scale of this controversy could render the testing model incomprehensible for the target population. If that were the case, the researchers would seek recommendations of the SAB regarding the necessary changes to the trial model. In such a situation, the hydroxychloroquine arm could become the new control arm (in the absence of convincing evidence of efficacy), thus the relevance of the trial would be reduced. With consideration to the multi-arm model, a difference between hydroxychloroquine and one or the other of the experimental treatments would allow conclusions to be drawn on what would be the meaning of such a difference. Any absence of difference, however, would not be very informative and not allow any conclusions.

Within this population, the issue of multiple drug treatments, with their risks of interaction, cardiac toxicity induced by chloroquine and its derivatives, will be the subject of particular attention. ECG shall be systematic before inclusion, opinion from a cardiologist would be sought in cases of doubt and people included, yet considered as needing to be monitored on this point, would be provided with a self-monitoring ECG device with remote transmission.

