#### 1.4.4 Choice of studied population

As for all antiviral treatments, treatment for SARS-CoV-2 would have more chance of being efficacious, if it were administered as quickly as possible after symptoms onset. We have retained as an inclusion criterion “having experienced symptoms for fewer than 72 hours at the time of diagnostic testing”.

The main group of the main trial shall be made up of people not taking renin-angiotensin system blockers (ACEI or ARB) before inclusion, who would be randomised between the 5 arms of the study. Calculations for the scale of the study allow for the necessary ability to make comparisons within this group.

People taking renin-angiotensin system blockers (ACEI or ARB) before inclusion represent approximately 20% of patients of the target population for which the study shall be proposed. They cannot be randomised in the Telmisartan arm, but we did not wish to exclude them from the study. They shall therefore be randomised into the 4 other arms and constitute a separate group, which shall be analysed independently. The scale of the study within this group is based on the feasibility of recruitment, using the calculation of the scale of the study of the main group. An extension of the scale

of the study could be made after opinion from the SAB to allow sufficient statistical significance within this group. If the Telmisartan arm of the main group is abandoned in the course of the study on grounds of futility, then people taking renin-angiotensin system blockers (ACEI or ARB) are able to be randomised in the main trial.

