#### 4.2.1 Choice of treatments at the time of drafting the protocol

At the time of drafting this protocol:

- The people of the control arm shall receive a food supplement (AZINC Forme et Vitalité®) containing a complex of vitamins and trace elements, for which there is no reason to believe that they are active on the virus.
- Those experimental treatments retained are
  - hydroxychloroquine, favipiravir, imatinib and telmisartan, for people who were not taking renin-angiotensin system blockers (ACEI or ARB) before inclusion.
  - hydroxychloroquine, favipiravir and imatinib, for people who were under treatment by renin-angiotensin system blockers (ACEI or ARB) before inclusion.

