#### 5.1.2.4 Other medical histories

- Known hypersensitivity to one of the trial drugs or to one of its excipients, as well as to one of the following compounds: chloroquine and other 4-amino quinolines, amodiaquine, mefloquine, glafenine, floctafenine, antrafenine, ARB.
- Presence of one of the following illnesses reported by the person: hepatic porphyria, known obstructive hepatobiliary disease, liver failure (score  $\geq$  Child-Pugh B), chronic kidney disease stage 4 or 5 (GFR  $<30$  mL/min/1.73 m^2) or dialysis, retinopathy, lactose hypersensitivity, anomalies in galactose metabolism, lactase deficiency, malabsorption syndrome, known glucose-6-phosphate-dehydrogenase deficiency, symptomatic gout/hyperuricemia.

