### 5.2.6 Concomitant drugs

Drugs whose taking is indicated as a criterion for non-inclusion (please see paragraph **Erreur ! Source du renvoi introuvable.**) shall be contra-indications of prescription over the 10 days following inclusion.

In all the arms, the usage rules for additional drugs that could be taken for symptomatic purposes, including paracetamol, shall be explained. A prescription for such treatments could be drawn up by the Doctor of the mobile study team, in close collaboration with the attending physician. For participants without any possibility of having third parties collect these drugs from the chemist's, the mobile study team, in collaboration with the attending physician, shall make the appropriate provisions.

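### Current, recent or on-study use of hydroxychloroquine, imatinib or favipiravir outside allocation breaches no listed rule, so controls may be taking a drug under test

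*Protocol*

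**What the plan says.** Protocol 4.2.1 names the experimental treatments as "hydroxychloroquine, favipiravir, imatinib and telmisartan, for people who were not taking renin-angiotensin system blockers (ACEI or ARB) before inclusion", with the first three also offered to people who do take those blockers.

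Drug-related eligibility is set in 5.1.2.3 by two lists. The first has a look-back: "Treatment in progress or taken in the last 30 days by one of the following drugs: piperazine, halofantrine, dasatinib or nilotinib". The second concerns current use only and begins "Treatment in progress by: citalopram, escitalopram, hydroxyzine, domperidone, powerful inhibitors of the CYP3A4 isoenzyme of the P450 cytochrome", followed by strong CYP3A4 inducers. The exclusion criteria in the summary merge the two, starting "Treatment with piperazine, halofantrine, dasatinib, nilotinib, citalopram, escitalopram, hydroxyzine, domperidone", and add further drugs. No trial drug appears in any of these lists. The trial drugs enter the non-inclusion criteria only through allergy, in 5.1.2.4: "Known hypersensitivity to one of the trial drugs or to one of its excipients".

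Section 5.2.6 defines the drugs barred for the 10 days after inclusion by reference back: "Drugs whose taking is indicated as a criterion for non-inclusion".

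For telmisartan's class the protocol does act on prior use. Section 1.4.4 says of ACEI/ARB users: "They cannot be randomised in the Telmisartan arm, but we did not wish to exclude them from the study". Section 4.4 gives them a separate randomisation list.

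Section 6.1 makes every primary-endpoint analysis intention-to-treat with missing counted as failure. On-treatment, per-protocol and as-treated analyses are secondary variants in 6.3.4.

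**The concern.** The comparison assumes that controls do not receive the drug under test. The written rules do not secure this for three of the four drugs. Someone already taking hydroxychloroquine can be allocated to control, to another experimental arm, or to the arm that supplies it. A participant prescribed it after randomisation breaches nothing listed in 5.2.6. Imatinib is the odd omission: 5.1.2.3 excludes two other named drugs over 30 days but not imatinib, which 1.3.3 describes as a long-standing chronic treatment with many elderly users.

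Exposure in the control arm pulls that drug's observed difference towards zero. Power falls, and the three futility looks become more likely to discard a treatment that works. Because the primary analysis follows allocation, nothing done at analysis restores the contrast in the primary result.

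**Working it through.** **Reading the rules together**

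| Drug under test | Prior use addressed? | Use outside allocation during the 10 days addressed? |
|---|---|---|
| Telmisartan | Yes, ACEI/ARB users have a separate list (1.4.4, 4.4) | No, ACEI/ARB use is not a non-inclusion criterion |
| Hydroxychloroquine | No | No |
| Imatinib | No | No |
| Favipiravir | No | No |

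Three other provisions come near but do not close the gap. The treatment review at inclusion (5.3.3) checks treatments against criteria that omit these drugs. The bar on other studies (summary) covers interventional research, not ordinary prescription. The remote visits (5.3.5) record concomitant treatments without prohibiting any.

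**Inputs for the size of the effect**

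From 6.2.1: control rate 25%; target a halving, so 12.5%; power 80%; one-sided tests; 169 per arm; futility thresholds 0.65, 0.45 and 0.25 at 30, 60 and 102 per arm; O'Brien-Fleming efficacy looks at 102 and 169. The total efficacy alpha is not given as a number for those two looks, so 0.025 and 0.05 were both tried. The share of exposed controls, c, is not in the protocol and is assumed.

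**Reproducing the plan's own figure**

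Normal-approximation power for 25% against 12.5% is 95.0% at 30 per arm (alpha 0.65), 95.1% at 60 (0.45) and 94.9% at 102 (0.25), so each futility stage has about 95% power.

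The whole pairwise comparison was then simulated (400,000 runs, pooled z test, binding futility, O'Brien-Fleming-type spending at information 102/169). With total one-sided alpha 0.025 the efficacy bounds are z = 2.66 and 1.98, and power at 169 per arm is 80.2%. With 0.05 it is 85.2%. The stated 169 is therefore reproduced at 0.025.

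**Effect of exposed controls**

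If exposed controls get the drug's full effect:

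control rate = 25% − c × (25% − 12.5%) = 25% − 12.5c points

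For example, c = 0.10 gives 25 − 1.25 = 23.75%.

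| c (assumed) | Control rate | Power, alpha 0.025 | Power, alpha 0.05 | Wrongly stopped for futility |
|---|---|---|---|---|
| 0 | 25.00% | 80% | 85% | 9.8% |
| 2% | 24.75% | 79% | 84% | 10.5% |
| 5% | 24.38% | 77% | 82% | 11.4% |
| 10% | 23.75% | 72% | 79% | 13.3% |
| 20% | 22.50% | 63% | 71% | 17.6% |

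The last column is the chance that an arm with a true halving is dropped at any of the three futility looks.

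Recruiting more would be the expensive remedy. The fixed-design sizes at one-sided 0.05 and 80% power are 120, 131, 144 and 178 per arm at c = 0, 5, 10 and 20%. Scaling 169 by their ratios gives about 169 × 131/120 = 184, 169 × 144/120 = 203 and 169 × 178/120 = 251 per arm.

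**The case against.** - **Crossover is not ignored.** The control arm is described as standard of care (4.2), concomitant treatments are recorded (5.3.5), and per-protocol and as-treated sets are defined in section 6. This stands, but those analyses are secondary and lose the protection of randomisation.
- **Other criteria remove some users.** Severe chronic illness with limited life expectancy (5.1.2.1), the ECG rules (5.1.2.2) and retinopathy (5.1.2.4) exclude some chronic users, and ACEI/ARB users cannot enter the telmisartan arm. A reader might infer that any user of a trial drug can enter every arm. That is too broad.
- **The rate may be small.** A reader might infer that contamination is likely, because 1.4.3 says of hydroxychloroquine that "it is actually possible that the scale of this controversy could render the testing model incomprehensible for the target population". That sentence concerns whether the design can be understood, not what controls will take. Sections 1.4.3 and 4.2.2 also plan a response through the scientific board and an amendment. Symptoms must have begun less than 72 hours before the swab, which limits time for self-treatment. Any expectation of use is an inference, best grounded for hydroxychloroquine and weak for favipiravir.
- **A larger baseline should not be used.** A fixed one-sided 0.05 test at 169 per arm gives about 91% power, but it ignores the futility looks and is not this trial's design.
- **A bare addition to the exclusion list would backfire.** Section 5.2.6 contra-indicates whatever the non-inclusion criteria name. Read literally, adding the three drugs would contra-indicate the allocated treatment in three arms. This objection stands and shapes the remedy.

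**Conclusion.** The gap is real and lies in the protocol's own rules on eligibility and concomitant drugs, which an analysis plan cannot change. Following them exactly permits a dilution that the protocol guards against at entry for telmisartan's class only.

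Its size is uncertain. At 2% of controls exposed, power drops by about one point. At 10% it drops by 6 to 8 points depending on the total alpha, and wrongful futility stops rise from 9.8% to 13.3%. At 20%, power is about 63% at alpha 0.025. These figures rest on an assumed exposure rate, on exposed controls getting the full effect, on a true halving from 25%, and on binding futility rules. They describe one drug's comparison at a time.

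The sample size of 169 is not in error. It assumes unexposed controls. The point is worth correcting because correction before enrolment is cheap and the primary analysis cannot repair the dilution afterwards.

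**What to change.** Reconcile 5.1.2.3, the summary's exclusion list and 5.2.6 with the treatment list in 4.2.1 and 5.2:

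1. State in the eligibility criteria how current or recent use of a trial drug is handled, naming hydroxychloroquine or chloroquine, imatinib and favipiravir. The look-back and the exact rule are for the sponsor to set.
2. Word 5.2.6 separately, so that it addresses trial drugs taken outside the allocated arm and cannot be read as contra-indicating the allocated treatment. Say whether it also covers starting telmisartan's class after inclusion.
3. Classify such use as a protocol deviation and record it through the treatment review at inclusion (5.3.3) and the concomitant-treatment questions at the remote visits (5.3.5).

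The cost is wording in three places and a small number of chronic users who may become ineligible. No new visit or procedure is needed.
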